# Intact Fish Skin Graft vs. Standard of Care in Patients with Neuroischaemic Diabetic Foot Ulcers (KereFish Study): An International, Multicentre, Double-Blind, Randomised, Controlled Trial Study Design and Rationale

**DOI:** 10.3390/medicina58121775

**Published:** 2022-12-01

**Keywords:** diabetes foot ulcer, cell and/or tissue-based wound care products, intact fish skin graft

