## 2. Materials and Methods

This study, KereFish, is the French part of a multinational clinical trial taking place in France, Germany, Italy, and Sweden. The overarching study, Odin, is a multi-national, multicentric, randomised, controlled, open-label, interventional study comparing the use of Kerecis Omega3 Wound with conventional therapy (SOC, Standard of Care) in the treatment of complex, hard-to-heal, diabetic foot wounds with a planned total of 330 patients.

Primary objective: To demonstrate the superiority of Kerecis Omega3 Wound over SOC in the treatment of severe diabetic wounds with or without a moderate arterial component.

Secondary objectives: The secondary objectives are to: (i) Evaluate the safety of Kerecis Omega3 Wound. (ii) Assess secondary clinical efficacy endpoints. (iii) Assess patient and caregiver satisfaction. (iv) Assess the impact on patient quality of life. (v) Assess the economic impact of Kerecis Omega3 Wound treatment on patient care costs and to determine the effectiveness of this treatment.

Primary endpoint: Percentage of healed wounds with complete epithelialisation at 16 weeks.

Secondary endpoints: Change in ulcer grade according to the University of Texas diabetic wound classification at each weekly visit. Change in quality of life. Change in pain. Healing trajectory. Cost effectiveness. Number of participants with fully healed ulcers at 20 weeks. Number of participants with fully healed ulcers at 24 weeks. Percentage of ulcers healed 50% or more at 12 weeks.

Inclusion criteria: People living with diabetes of any age with diabetic foot ulcer Grade 2 or 3 according to the University of Texas (UT) diabetic foot classification system [13]; Grade 2: wound penetrating to the tendon or capsule. UT Grade 3: wound penetrating to bone or joint, OR patients admitted/ambulatory for diabetic foot wounds or amputations, which have not closed or are dehiscent. Patients who can tolerate aggressive surgical debridement. Patients without severe ischaemia; ankle brachial index (ABI) > 0.6 or big toe pressure > 50 mmHg if ABI is not possible. Wound age ≥ 30 days (does not apply to amputation wounds; patients can be included when the wound is less than 30 days old) or if the amputation level is below the ankle. Patients willing and able to give informed consent to participate in the clinical trial. Male or female over 18 years of age. Patients living at a geographical distance compatible with the home nurse.

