### 2.1. Conduct of the Study

This study uses the Smart-Trial^®^ electronic platform for gathering data, obtaining CRFs, and monitoring of the study. The study design is demonstrated in Figure 1. Randomisation will take place after inclusion via the electronic case report form. The randomisation list is in blocks of two; the stratification will be performed according to two criteria: amputation and non-amputation wounds and ABI (≤0.9 and >0.9). Patients will then be assigned either to the conventional treatment group (control group), or to the interventional group, where they will be treated with Kerecis Omega3 Wound. The hospital investigator will assess the wound status of patients in both groups during hospital visits at the following times:Week 7: patients come to the hospital for the investigator to assess wound progress.Week 16: end of study visit after the last application of Kerecis Omega3 Wound. An HbA1c measurement will be collected.Week 20: patients come to the hospital for the investigator to assess the progress of the wound.Week 24: at the end of the two-month follow-up period an HbA1c measurement will be collected.

The referral nurse (RN) and the home nurses (HNs) for the study in each centre will receive theoretical and practical training from a Kerecis professional specialized in wound care.

In the study, the difference between the standard of care group and the interventional group is that Kerecis Omega3 Wound is applied between the dressing, that would otherwise contact the ulcer, and the ulcer bed. The dressing on top of Kerecis Omega3 Wound then becomes the covering dressing. In the control group, the care is the same whilst there is no Kerecis Omega3 Wound under the covering dressing. Most often, the covering dressing would be a foam dressing. The different approaches for using offloading in different clinics will adhere to the International Working Group on the Diabetic Foot’s Guidelines [10].

Kerecis Omega3 Wound is applied once per week for the first six weeks, and every other week for the remaining 8 weeks of active intervention, with up to 10 applications in total. If complete epithelialization is achieved, the application will be stopped. Both groups will receive standard of care for the last two weeks (Weeks 15 and 16). For both groups each week, when the home nurse takes a picture of the wound, he/she will ask the patients to fill in a visual analogue scale (VAS) for perception of pain.

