### 2.3. Photography

The ulcer is photographed before debridement/cleaning, after debridement/cleaning if that is deemed necessary, and after placement of Kerecis Omega3 Wound (if applicable) with a centimetre scale and patient identifier placed in the photo. An acetate tracing (outline of the ulcer on transparent plastic) is made and photographed where a centimetre scale and a patient identifier is visible in the photo. Photos are uploaded via the Smart-Trial^®^ portal as a part of filling out the case report form). The largest diameter, and the diameter perpendicular, is measured at all visits.

Three status checkpoints are imbedded in the study:i.Has the wound changed its grade, i.e., have the granulations covered bone and tendon? Answered by clinician since the answer is dependent on probing to bone.ii.Is the wound ready for standard of care only, to commence healing? Answered by clinician and blinded panel of clinicians.iii.Would a split thickness skin graft be a logical next intervention? Answered by blinded panel only.

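### The title calls the trial double-blind but the methods make it open-label, and no blinded reading of the week-16 primary endpoint is described

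*Protocol article*

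**What the plan says.** The protocol article makes two incompatible statements about blinding.

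- **Title:** "An International, Multicentre, Double-Blind, Randomised, Controlled Trial Study Design and Rationale".
- **Section 2 (Materials and Methods):** "This study, KereFish, is the French part of a multinational clinical trial", and "The overarching study, Odin, is a multi-national, multicentric, randomised, controlled, open-label, interventional study".

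The abstract calls the trial randomised and controlled and does not mention blinding.

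Section 2.1 sets out how the arms differ. The graft lies between the ulcer bed and the dressing in one arm. For the other arm: "In the control group, the care is the same whilst there is no Kerecis Omega3 Wound under the covering dressing". No sham is described.

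The primary endpoint (section 2) is complete epithelialisation at 16 weeks. On who looks at the wound, section 2.1 says "The hospital investigator will assess the wound status of patients in both groups during hospital visits", and lists weeks 7, 16, 20 and 24.

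Section 2.3 (Photography) contains the only blinding described in the body of the article. Of three status checkpoints, the second (whether the wound is ready for standard care alone) is "Answered by clinician and blinded panel of clinicians". The third (whether a split-thickness skin graft would be logical) goes to the blinded panel only. Section 2.4 names no assessor for the primary endpoint.

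**The concern.** A reader who sees double-blind in a title takes it that patients, carers and assessors do not know the arm, and discounts assessment bias accordingly. Here the stated design does not support that.

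It matters because complete epithelialisation is a yes/no clinical judgement, and some wounds will be borderline. An assessor who knows that a wound carried the graft could, without intending to, resolve doubtful cases in its favour. In a superiority trial that could inflate both the apparent effect and the false-positive rate. The article does have a blinded panel, but the questions it assigns to that panel do not include the one on which the trial will be judged.

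**Working it through.** **1. The title against the methods.** KereFish is part of Odin (section 2), so Odin's design label applies to it. The title says double-blind and section 2 says open-label. Both are current text, and they cannot both hold. Section 2.1 shows which is wrong: a graft against no graft, without a sham, and nothing described that would mask patients, nurses or investigators.

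**2. Who judges the primary endpoint.**

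| Question | Named assessor | Where |
|---|---|---|
| Wound status at weeks 7, 16, 20, 24 | Hospital investigator | Section 2.1 |
| Checkpoint i: change of grade | Clinician | Section 2.3 |
| Checkpoint ii: ready for standard care alone | Clinician and blinded panel | Section 2.3 |
| Checkpoint iii: skin graft logical | Blinded panel only | Section 2.3 |
| Complete epithelialisation at week 16 | Not stated | Sections 2 and 2.4 |

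The investigator is the only assessor named at week 16. That this assessor knows the arm follows from the open-label label; it is not stated separately.

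**3. How much bias could matter.** The article gives no figure on blinding to reproduce, so this is an illustration.

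Inputs from section 2.4: two-sided Fisher's exact test at 0.05, 90 per group, 30% healing under standard care. Assumed, and not in the documents: true healing is 30% in both arms, and a fraction f of unhealed wounds is called healed.

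Observed healing in an arm = 0.30 + 0.70 × f. The rejection rate is the sum, over all pairs of healed counts (x, y) from 0 to 90, of Binomial(x; 90, p_control) × Binomial(y; 90, p_graft) wherever Fisher's p ≤ 0.05.

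| f, control | f, graft | Observed healing | Rejection rate |
|---|---|---|---|
| 0 | 0 | 30.0% vs 30.0% | 3.4% |
| 0 | 5% | 30.0% vs 33.5% | 5.8% |
| 0 | 10% | 30.0% vs 37.0% | 13.3% |
| 0 | 15% | 30.0% vs 40.5% | 26.6% |
| 5% | 10% | 33.5% vs 37.0% | 5.8% |
| 10% | 10% | 37.0% vs 37.0% | 3.6% |

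The one-sided 10% case is a 7-point shift, or 90 × 0.07 = 6.3 wounds. Of its 13.3 percentage points of rejections, 13.2 favour the graft.

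The same calculation at 30% against 50% gives 74.9% power, where section 2.4 states 80%. That is a separate matter and does not bear on blinding.

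**The case against.** The title contradiction has no good defence. The rest can be challenged on four grounds.

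- **The assessor is inferred.** A reader might conclude that the primary outcome rests with an unblinded investigator. The article does not say so. It says who assesses wound status at the visits, not whose reading decides the endpoint, and an open-label trial can still have blinded endpoint reading. The article condenses a fuller protocol that may assign it. This stands, so the point is limited to what is described.
- **The panel's role and material are inferred.** A reader might also take it that the panel reads the uploaded photographs and is confined to two questions. Its place in the Photography section suggests the former, but the text states neither. This stands too.
- **The error rates are hypothetical.** The model puts all misreading in the graft arm and in its favour. With 10% against 5% the rejection rate is 5.8%, and with 10% in both arms it is 3.6%. The table therefore shows what a difference between arms could do. It is not evidence that such a difference exists here.
- **A panel read is not free of difficulty.** Photographs after cleaning are taken only when judged necessary (section 2.3). After healing, home-nurse visits stop and photographs become monthly (section 2.2). Inclusion ended in July 2022 (abstract). Sixteen weeks (112 days) after 31 July is 20 November 2022, before the article's publication date of 1 December 2022, so a panel read would be retrospective. These limits shape the remedy but do not rule it out.

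**Conclusion.** The title is wrong as written and must be corrected. That rests on the article's own text and on no assumption.

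The second part is narrower. As described, the only assessor named at the primary time point is the investigator in an open-label trial, and the blinded panel is not stated to judge complete epithelialisation. The documents do not support saying that no blinded adjudication exists.

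If the investigator's reading does decide the endpoint, the false-positive rate could rise from 3.4% to 5.8%, 13.3% or 26.6% when 5%, 10% or 15% of unhealed graft-arm wounds are misread and no control wounds are. It depends on the difference between arms, and equal misreading removes almost all of the rise. Confidence is high on the title and moderate on the assessor.

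**What to change.** 1. **Title.** Replace double-blind with open-label. Add that outcome assessment is blinded only if that is true of the primary endpoint.
2. **Assessor.** State who adjudicates complete epithelialisation at week 16 and whether that reading is blinded. If the full protocol already assigns it to the panel, saying so settles the point.
3. **Otherwise, a blinded read.** Have the existing panel answer yes or no on complete epithelialisation from the stored week-16 photographs. For early healers, use the monthly follow-up photograph nearest week 16. Withhold every photograph taken after graft placement, since it reveals the arm. Section 2.1 has both groups on standard care alone in weeks 15 and 16, which should limit such cues at week 16.
4. **Status of that read.** Specify it before any analysis by arm. Make it the primary endpoint if an amendment is still possible before analysis. If not, report it as a prespecified sensitivity analysis beside the investigator's reading.

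The cost is a wording change, one more question for an existing panel, and the work of a retrospective read. The downside is that some photographs may be missing or unreadable. Report their number and handling by arm. Falling back on the investigator's reading for them would return a judgement made with knowledge of the arm to the endpoint, so the rule should be fixed in advance.

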## Abstract

Background: Cell and/or tissue-based wound care products have slowly advanced in the treatment of non-healing ulcers, however, few studies have evaluated the effectiveness of these devices in the management of severe diabetic foot ulcers. Method: This study (KereFish) is part of a multi-national, multi-centre, randomised, controlled clinical investigation (Odin) with patients suffering from deep diabetic wounds, allowing peripheral artery disease as evaluated by an ankle brachial index equal or higher than 0.6. The study has parallel treatment groups: Group 1 treatment with Kerecis^®^ Omega3 Wound™ versus Group 2 treatment with standard of care. The primary objective is to test the hypothesis that a larger number of severe diabetic ulcers and amputation wounds, including those with moderate arterial disease, will heal in 16 weeks when treated with Kerecis^®^ Omega3 Wound™ than with standard of care. Conclusion: This study has received the ethics committee approval of each participating country. Inclusion of participants began in March 2020 and ended in July 2022. The first results will be presented in March 2023. The study is registered in ClinicalTrials.gov as Identifier: NCT04537520.

## 1. Introduction

While the prevalence of diabetes is increasing in developed countries, the quality of management of diabetes is improving and consequently, the cost of management is also increasing [1,2]. Rates of diabetes-related complications have declined substantially, but a large burden of the disease persists because of the continued increase in the prevalence of diabetes and cost of management of diabetes complications is also increasing [1,2,3]. Diabetic foot complications are serious and costly [4]. Diabetic foot ulcer (DFU) most often results from the combination of two major complications of diabetes: diabetic neuropathy and angiopathy, often complicated by soft tissue and bone infection. Arterial disease represents the most severe prognosis in terms of amputation and mortality. DFUs are a severe complication of diabetes mellitus and impact morbidity, mortality, and healthcare expenditure in a serious way. It is known that that 19–34% of patients with diabetes are likely to be affected with a DFU in their lifetime, and the International Diabetes Federation reports that 9.1–26.1 million people will develop DFUs annually [5]. Patients with DFUs were also found to have a 2.5-fold increased risk of death compared with their diabetic counterparts without foot wounds [6]. Treatment of DFUs accounts for approximately one-third of the total cost of diabetic care, which was estimated to be USD 176 billion in direct healthcare expenditures in 2012 [7]. Despite these high healthcare costs, about 20% of patients have unhealed DFUs at 1 year [8]. Even after wound resolution, subsequent DFUs are common, with a recurrence rate of roughly 40% of patients within 1 year [5]. Although there are well-established principles for managing DFUs, it is always a challenge. The fundamental care of a DFU includes sharp debridement, off-loading, and diabetic foot education in addition to local wound care with or without surgical debridement, dressings promoting a moist wound environment, wound off-loading, vascular assessment, general medical assessment, treatment of infections, and glycaemic control [9,10]. Thus, diabetic foot care must be multidisciplinary.

Cell and/or tissue based wound treatment products (CTPs) have slowly been advancing in the treatment of non-healing ulcers in the last 20 years. The first large studies on CTPs were published in 2005 for use on venous leg ulcers [11]. The largest of these studies used material from pig small intestine in the intervention group and later a number of other materials have been studied and used, mainly decellularized membranous organs from mammals but also cellularised skin equivalents and freeze dried amnionic membranes. In 2013, a new product was approved in the US by the Food and Drug Administration, decellularized fish skin [Kerecis^®^ Omega3 Wound™, Kerecis, Iceland]. Delivered as a sterilized, freeze-dried material, the fish skin graft has the benefit of not being treated with antibiotics and virus inactivating methods, thereby allowing the natural omega-3 fatty acids to remain, and it is a by-product of the food industry. Therefore, the fish derived CTP is both ecologically sustainable as well as rich in naturally occurring soluble molecules and omega-3 fatty acids. Omega-3 fats seem to have a multitude of positive actions, including an anti-inflammatory function and to some extent anti-bacterial properties. In clinical use it has promoted healing of chronic ulcers [12], consequently, its evaluation in the treatment of DFU is legitimate.

## 2. Materials and Methods

This study, KereFish, is the French part of a multinational clinical trial taking place in France, Germany, Italy, and Sweden. The overarching study, Odin, is a multi-national, multicentric, randomised, controlled, open-label, interventional study comparing the use of Kerecis Omega3 Wound with conventional therapy (SOC, Standard of Care) in the treatment of complex, hard-to-heal, diabetic foot wounds with a planned total of 330 patients.

Primary objective: To demonstrate the superiority of Kerecis Omega3 Wound over SOC in the treatment of severe diabetic wounds with or without a moderate arterial component.

Secondary objectives: The secondary objectives are to: (i) Evaluate the safety of Kerecis Omega3 Wound. (ii) Assess secondary clinical efficacy endpoints. (iii) Assess patient and caregiver satisfaction. (iv) Assess the impact on patient quality of life. (v) Assess the economic impact of Kerecis Omega3 Wound treatment on patient care costs and to determine the effectiveness of this treatment.

Primary endpoint: Percentage of healed wounds with complete epithelialisation at 16 weeks.

Secondary endpoints: Change in ulcer grade according to the University of Texas diabetic wound classification at each weekly visit. Change in quality of life. Change in pain. Healing trajectory. Cost effectiveness. Number of participants with fully healed ulcers at 20 weeks. Number of participants with fully healed ulcers at 24 weeks. Percentage of ulcers healed 50% or more at 12 weeks.

Inclusion criteria: People living with diabetes of any age with diabetic foot ulcer Grade 2 or 3 according to the University of Texas (UT) diabetic foot classification system [13]; Grade 2: wound penetrating to the tendon or capsule. UT Grade 3: wound penetrating to bone or joint, OR patients admitted/ambulatory for diabetic foot wounds or amputations, which have not closed or are dehiscent. Patients who can tolerate aggressive surgical debridement. Patients without severe ischaemia; ankle brachial index (ABI) > 0.6 or big toe pressure > 50 mmHg if ABI is not possible. Wound age ≥ 30 days (does not apply to amputation wounds; patients can be included when the wound is less than 30 days old) or if the amputation level is below the ankle. Patients willing and able to give informed consent to participate in the clinical trial. Male or female over 18 years of age. Patients living at a geographical distance compatible with the home nurse.

### 2.1. Conduct of the Study

This study uses the Smart-Trial^®^ electronic platform for gathering data, obtaining CRFs, and monitoring of the study. The study design is demonstrated in Figure 1. Randomisation will take place after inclusion via the electronic case report form. The randomisation list is in blocks of two; the stratification will be performed according to two criteria: amputation and non-amputation wounds and ABI (≤0.9 and >0.9). Patients will then be assigned either to the conventional treatment group (control group), or to the interventional group, where they will be treated with Kerecis Omega3 Wound. The hospital investigator will assess the wound status of patients in both groups during hospital visits at the following times:Week 7: patients come to the hospital for the investigator to assess wound progress.Week 16: end of study visit after the last application of Kerecis Omega3 Wound. An HbA1c measurement will be collected.Week 20: patients come to the hospital for the investigator to assess the progress of the wound.Week 24: at the end of the two-month follow-up period an HbA1c measurement will be collected.

The referral nurse (RN) and the home nurses (HNs) for the study in each centre will receive theoretical and practical training from a Kerecis professional specialized in wound care.

In the study, the difference between the standard of care group and the interventional group is that Kerecis Omega3 Wound is applied between the dressing, that would otherwise contact the ulcer, and the ulcer bed. The dressing on top of Kerecis Omega3 Wound then becomes the covering dressing. In the control group, the care is the same whilst there is no Kerecis Omega3 Wound under the covering dressing. Most often, the covering dressing would be a foam dressing. The different approaches for using offloading in different clinics will adhere to the International Working Group on the Diabetic Foot’s Guidelines [10].

Kerecis Omega3 Wound is applied once per week for the first six weeks, and every other week for the remaining 8 weeks of active intervention, with up to 10 applications in total. If complete epithelialization is achieved, the application will be stopped. Both groups will receive standard of care for the last two weeks (Weeks 15 and 16). For both groups each week, when the home nurse takes a picture of the wound, he/she will ask the patients to fill in a visual analogue scale (VAS) for perception of pain.

For the management of wounds in the conventional group, a specific care protocol will be communicated to those involved in the patient’s care. This protocol will include indications for the following elements of wound care: (i) Cleaning: basic hygiene care, Isotonic saline solution, running water and neutral soap. (ii) Debridement (aggressive, surgical) of the wound will be mechanical using a fixed blade scalpel/scalpel No. 10 or 15, or a sterile single-use curette such as MediSet^®^. The debridement procedure will be performed from the centre to the periphery of the lesion by removing non-vital components in the tangential planes and removing overhanging edges and hyperkeratosis and acanthosis of the skin at the wound edges. Mild bleeding attests to the quality of the debridement. (iii) Recovery: various dressings can be used: hydrocolloids, hydrofibres, alginate, hydrocellular and charcoal dressings, silver dressings, wound contact dressings, including fatty tulle (Vaseline gauze) and compression dressings (postoperative indication). Practical Guidelines on the prevention and management of diabetic foot disease of the International Working Group on the Diabetic Foot (IWGDF) are also used for choice of the local recovery [10].

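### Blocks of two in an open-label trial are the most predictable 1:1 choice; the resulting exposure to selection bias ranges from slight to serious, depending on facts the article does not give

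*Protocol article*

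**What the plan says.** Protocol article, section 2.1 (Conduct of the Study): "The randomisation list is in blocks of two". No second block size and no random variation is mentioned. The same section says that "the stratification will be performed according to two criteria: amputation and non-amputation wounds and ABI (≤0.9 and >0.9"), which makes four strata; centre is not named. On timing and route: "Randomisation will take place after inclusion via the electronic case report form".

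On blinding, section 2 (Materials and Methods) describes Odin, of which KereFish is the French part, as a "randomised, controlled, open-label, interventional study comparing the use of Kerecis Omega3 Wound with conventional therapy". The title instead reads "International, Multicentre, Double-Blind, Randomised, Controlled Trial Study Design and Rationale". In section 2.1 the control arm is described so that "the care is the same whilst there is no Kerecis Omega3 Wound under the covering dressing", and no sham is mentioned. The only blinded role is a panel that answers two of the three status checkpoints in section 2.3 (Photography); for one of these the entry is "Answered by clinician and blinded panel of clinicians".

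**The concern.** In a 1:1 block of two, the second allocation is always the opposite of the first. Treating staff see which arm the first patient received, because the graft is either there or not. Amputation status and ABI are known before inclusion, so the clinician also knows which stratum list the next patient will draw from. Someone who can follow that list can infer the next arm and let it influence whether, or when, to include a patient.

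Eligibility runs from UT grade 2 to grade 3 and includes unclosed amputation wounds and a range of ABI, so there is room to select on prognosis. If better-prognosis patients were entered when the graft was expected, the difference in healing would be biased. Blinded assessment afterwards would not remove that bias, because it arises at enrolment.

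**Working it through.** The article gives no figure for predictability, so there is none to reproduce.

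**Inputs from the article.** Block size 2; four strata (2 × 2); 180 randomised; 90 per group; Fisher's exact test, two-sided 0.05; healing 30% against 50% (sections 2.1 and 2.4).

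**Assumptions, not in the article.** Number of centres c, taken as 5 or 10, recruiting equally; a shift η in healing probability of the patients steered, taken as 5 or 10 points; mean healing 40%, the midpoint of 30% and 50%; no true treatment effect.

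**1. Share of allocations that are certain, given the earlier ones on a list that can be followed.** For block size b the share is 1/(b/2 + 1). Enumerating all permuted blocks also gives the share guessed correctly by always naming the arm that is behind:

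| Known fixed block size | Certain | Guessed correctly |
|---|---|---|
| 2 | 1/2 = 50% | 75% |
| 4 | 1/3 = 33.3% | 70.8% |
| 6 | 1/4 = 25% | 68.3% |

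With 180 patients and blocks of two, up to 180 × 0.5 = 90 allocations are certain. The guessing rate falls only slowly with a larger known size, so random variation and non-disclosure matter as well as size.

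**2. Lists kept per centre (upper extreme).** Half of each arm sits in predictable slots. If every such slot is steered by ±η, each arm's mean moves by η/2 in opposite directions, and the difference moves by 0.5 × 2η = η. Exact Fisher rejection rate, 90 per arm:

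| η | Rates compared | Type I error |
|---|---|---|
| 0 | 40% v 40% | 3.7% |
| 5 points | 37.5% v 42.5% | 8.3% |
| 10 points | 35% v 45% | 23.6% |

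Centring on the protocol's 30% control rate instead gives 3.4%, 8.5% and 25.8%.

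**3. Lists shared across c centres.** A site sees only its own patients. Its last patient in the stratum shares a block with its next one with probability (1/c) × (1/2) = 1/(2c). Otherwise the guess is a coin toss, and the site cannot tell which case applies. Naming the opposite of its last patient's arm is therefore right with probability

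1/(2c) + (1 − 1/(2c)) × 1/2 = 1/2 + 1/(4c).

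- c = 5: 0.5 + 0.05 = 55%
- c = 10: 0.5 + 0.025 = 52.5%

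Simulation with 46 patients per stratum gives 56% and 53%.

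If every patient is steered on a guess that is right with probability q, the bias is 2η(2q − 1). With q = 1/2 + 1/(4c) this equals η/c. At c = 5, steering by 5 or 10 points gives 5/5 = 1 or 10/5 = 2 points of bias. The exact Fisher type I error is then about 3.9% or 4.4% (90 per arm, mean 40%), below the nominal 5%.

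**4. What a first-in-block analysis can show.** First positions number 180/2 = 90, about 45 per arm. Exact Fisher power for 30% against 50% at 45 per arm is about 41%.

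**The case against.** The strongest reply is that the deciding fact is absent. Only amputation and ABI are named as stratification criteria, which points to four lists shared across centres through the electronic case report form. On that reading a site's guess is only a few points better than chance. This stands, and it rules out a stronger statement that a reader might infer: that staff knew every second allocation with certainty, or that concealment failed. Certainty needs a list that can be followed. The article does not say that lists ran per centre, or that sites knew the block size.

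A reader might also infer that publishing the block size gave it away. It could not have done so for KereFish: the article is dated December 2022 and inclusion ended in July 2022. Nor do the documents show that any bias occurred. The steering sizes are assumptions, and the 8.3% and 23.6% figures need per-centre lists with every predictable slot steered in one direction.

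Two defences do not hold. Randomising electronically after inclusion hides the list, but it does not stop someone who infers the next arm from choosing whether or when to include. The double-blind wording in the title does not help either, because the text says open-label and blinds nobody who enrols or treats.

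It is also fair to say that a closed list cannot be changed and that the analysis plan is not shown. The point is therefore about the block size the article does state, and not about missing analyses.

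**Conclusion.** The point holds as a design weakness of moderate severity. Among 1:1 permuted blocks, a fixed size of two is the most predictable, and an open-label trial with a visible graft gives staff the information to use it. The exposure lies between two cases:

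- **Lists per centre:** up to 50% of allocations certain and 75% guessed correctly. Type I error is up to 8.3% or 23.6% if all predictable slots are steered by 5 or 10 points.
- **Lists shared, which the article's wording favours:** about 55-56% guessed correctly with 5 centres and 53% with 10. Type I error is about 3.9% to 4.4% at 5 centres under the same steering.

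Both cases rest on assumed steering and, for shared lists, on equally recruiting centres. The article does not settle which case applies.

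**What to change.** **Any part of Odin still randomising.** Generate the remaining list with larger, randomly varying block sizes, for example 4 and 6, and do not disclose them to sites. The article does not say whether any part is still open. The cost is a new list file in the electronic system and an imbalance of at most 2-3 patients per stratum (half of a block of 4 or 6).

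**KereFish, where inclusion has closed.**

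1. State whether lists ran per centre or were shared, and whether sites knew the block size. This shows which of the two cases applies and costs a sentence or two.
2. Before the outcome analysis, specify two sensitivity checks:
   - baseline wound area, UT grade, ABI and wound age by arm, separately for first and second block positions;
   - the primary risk difference in first-in-block patients, whose arm could not be inferred from earlier allocations on the list.

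These checks need the block positions from the list and about two lines in the analysis plan. With about 41% power, the second can support or question the main result but cannot replace it.

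**Blinding label.** Reconcile the title with the open-label description in section 2.
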